#### Daily assessments

Beginning at the quit date at week 1 throughout the duration of the 12-week intervention, we will use mobile-based daily assessments to validate abstinence and capture additional data related to stress and anxiety, urges to smoke, mood and physical symptoms, self-efficacy and confidence, motivation, tobacco and medication use, and diabetes information (Table 1). Daily assessments will be collected through the INSIGHT™ mobile health platform developed by OTRC [44]. We will purchase a Samsung Galaxy S7 phone in the US and a Samsung J3 Prime phone in the UK along with a 3-month data plan for each participant. Each participant will also receive a CoVita iCO™ Smokerlyzer® sensor to use throughout the study period. Using a smartphone application platform developed by the OUHSC OTRC mHealth Core, we programmed an app to collect our specific daily measures. The app will be installed onto the study phones and participants will be prompted through an evening alarm to submit daily CO readings (in ppm) and complete the daily assessment throughout the study period. The OUHSC mHealth Core has integrated the CO sensor into the platform with step-by-step instructions within the app that will collect assessment data so that participants will submit all measures in one cohesive assessment.

The daily assessment, estimated to take between 5 and 10 min, will begin with the CO reading followed by 5 items related to daily stress, which include the validated 4-item perceived stress scale [45]; 4 items assessing daily urges to smoke; the validated 12-item mood and physical symptoms scale [46]; 4 items related to self-efficacy, confidence, and motivation to quit; tobacco use, including products used, amount, and cessation medications; and 6 items related to diabetes management, which includes self-rated health, diabetes control, healthy food choices, and physical activity. Study coordinators will monitor compliance to daily assessments and will reach out to participants who quit completing assessments to encourage them to continue completing assessments.

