The incentives groups will have the opportunity to earn $20 or £15 per week by providing evidence of smoking abstinence using remote CO monitors. We will validate smoking abstinence via remote biochemical verification through the use of the CoVita iCO™ Smokerlyzer® breath monitor, which is a personal and remote CO sensor that plugs directly into a smartphone [37]. The iCO™ Smokerlyzer® has been demonstrated to be highly reproducible and able to differentiate between smokers and nonsmokers; however, results consistently differ slightly suggesting a need for calibration guidelines [38]. The OTRC has internally evaluated the validity and reliability of the iCO™ Smokerlyzer® integrated into the INSIGHT™ application by testing known concentrations of CO at 5 ppm, 10 ppm, and 20 ppm and found that multiple iCO™ Smokerlyzer® sensors were consistent and accurate enough to differentiate smokers from nonsmokers. Evidence of abstinence each week will be defined as 5 out of 7 days (> 70%) with CO readings of less than 8 parts per million (ppm) submitted through the remote CO sensor. Participants in the short-term incentives program will be eligible to earn weekly incentives for the first 6 weeks of the program, or only during the counseling portion of the usual care program. Participants in the long-term incentives program will be eligible to earn weekly incentives throughout the full duration of the 12-week usual care cessation program, which is the length of time they are eligible to receive NRT as part of usual care. Participants in both incentives groups will be notified weekly about incentives earned throughout the duration of follow-up, and earned incentives for both groups will be distributed in the form of gift cards at the end of the 13 week study (visit 3) following the return of the smartphone. Each weekly incentive is independent and does not require continuous abstinence throughout the entire incentive period. All three groups will be instructed to submit daily assessments for the duration of the 12-week program. Individuals in the control group will be unable to earn incentives and will not be compensated for their participation in the research study due to restrictions of the charity funding source. This is common in the UK and is not anticipated to be a problem. However, participants in the US are often compensated for research. Therefore, individuals in the US control group will be informed that they are eligible to win a tablet computer when they complete the 12-weeks and return the study phone.

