#### Exit surveys and interviews

At visit 3, participants will complete a brief exit survey that includes 10 questions related to their experience in the study. Participants will be asked to rate the difficulty or ease of using the smartphone, the app, and the CO device and about their perception of accuracy of the CO readings. They will be asked about reasons for missing daily assessments, the difficulty or ease of this quit attempt, whether payments may have helped them or could help others to quit, and if they were honest and completed the assessments themselves as instructed. The qualitative interviews will use semi-structured topic guides to gather rich and in-depth information related to the participants’ motivation to take part in the study, their attitudes towards financial incentives, their experiences in the study submitting data, their overall quit attempt, any perceived impact on their diabetes, and suggestions for improvements to the study. The interviews will be carried out in-person or over the telephone according to the participant’s preference and every participant will be approached for recruitment for an interview. The interviews will be audio-recorded and transcribed verbatim.

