#### Feasibility outcome measures

As this is a feasibility study, our primary outcomes will be the completion of the study protocol and proportion of daily assessments completed. Our secondary outcomes for the feasibility study will be monthly recruitment rates and participants’ acceptability of study procedures as measured in the exit survey and qualitatively in the exit interviews. Although this pilot study is underpowered to detect differences in cessation between groups, we will also measure and explore differences in the outcomes that would be used in a larger randomized controlled trial: continuous abstinence at 12 weeks, time to relapse, and cigarettes per day throughout the study period.

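### The daily session takes the CO reading before the tobacco-use items, and the article does not say when the ppm value is shown, so reported cigarettes per day may not be independent of the CO result

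*Protocol article*

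**What the plan says.** The section Daily assessments describes one evening session that "will begin with the CO reading followed by 5 items related to daily stress". It then lists urges, mood and physical symptoms, and self-efficacy and motivation. After these comes "tobacco use, including products used, amount, and cessation medications", followed by the diabetes items. The CO sensor is built into the app so that "participants will submit all measures in one cohesive assessment".

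Under Intervention and control groups, evidence of abstinence in a week is "defined as 5 out of 7 days (> 70%) with CO readings of less than 8 parts per million". Meeting that rule earns the weekly incentive in the short-term arm for the first 6 weeks and in the long-term arm for all 12. Controls earn nothing for CO results. Earnings are notified weekly and paid out at visit 3.

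Under Feasibility outcome measures, the cessation outcomes to be explored are "continuous abstinence at 12 weeks, time to relapse, and cigarettes per day throughout the study period". Table 2 lists cigarettes per day among the key secondary outcomes.

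Under Exit surveys and interviews, participants are asked about "their perception of accuracy of the CO readings". No section says whether, or at what moment, the app displays the reading.

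**The concern.** Cigarettes per day is self-reported and the trial is unblinded. If participants learn their ppm value and answer the tobacco items minutes later, the answer can be shaped by the result. Someone who smoked and sees a value below 8 ppm may leave cigarettes out. Someone who sees 8 ppm or more may feel there is nothing left to hide. The self-report then partly echoes the CO test instead of being a separate measurement.

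The CO result has a different meaning in each arm. Below 8 ppm it counts toward money in the incentive arms during their payment windows, and toward nothing in the control arm. An influence on self-report that differs by arm would enter the comparison of cigarettes per day. One stated aim is to obtain a likely effect size for a larger trial, so such an influence could be carried forward.

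**Working it through.** There is no sample-size or power figure to reproduce here. The check sets the sections side by side.

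**1. Order of items.** Item counts come from Table 1 and the order from Daily assessments:

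| Block | Items | Position |
|---|---|---|
| CO reading | 1 | 1 |
| Stress and anxiety | 5 | 2–6 |
| Urges | 4 | 7–10 |
| Mood and physical symptoms | 12 | 11–22 |
| Self-efficacy, confidence, motivation | 4 | 23–26 |
| Tobacco and medication use | 7 | 27–33 |
| Diabetes and health | 6 | 34–39 |

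Items between the CO reading and the tobacco block: 5 + 4 + 12 + 4 = 25. Total: 1 + 25 + 7 + 6 = 39. The exact positions assume that the list is the screen order. The point does not need that assumption: the session starts with CO, so every other item comes after it.

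**2. Source of cigarettes per day.** Table 1 marks the tobacco history questionnaire and the heaviness of smoking index at visit 1 only. A CO reading cannot give a cigarette count. The daily tobacco item is therefore the only listed source for cigarettes per day after the quit date. The article does not say outright that the outcome is taken from it.

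**3. Is the value seen, and when?** Two statements bear on this. Readings are submitted in ppm, but that may only name the unit of the data. The exit survey asks for perceived accuracy, which participants could hardly judge without having seen readings. Display at some point is therefore likely. Display before the tobacco items is possible but not stated.

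**4. What the result is worth, by arm.**

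| Weeks | Short-term | Long-term | Control |
|---|---|---|---|
| 1–6 | counts toward payment | counts toward payment | no payment |
| 7–12 | no payment | counts toward payment | no payment |

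A single reading does not settle payment. The week does, at 5/7 = 71.4% of days, consistent with the stated figure of more than 70%. The tobacco answers are not part of the rule.

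**5. Reach.** The primary outcomes are completion of the protocol and the proportion of daily assessments completed. Neither depends on whether the tobacco answer is true.

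**6. Size.** The documents give no share of smoking days, no share of those reading below 8 ppm and no rate of denial. Neither a size nor a direction can be calculated from them.

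**The case against.** The strongest reply is that the premise is not in the document. Screen behaviour is a detail that a journal article may leave to the full protocol, and if the app withholds the value until the session ends, the difficulty disappears. This stands in part: the point is conditional, and one sentence from the sponsor could close it.

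Second, payment rests on CO alone, so admitting a cigarette after a low reading costs nothing. This also stands. What remains is an indirect motive. Earnings are outstanding until visit 3, coordinators review the data weekly, and reporting cigarettes after a passing reading contradicts the evidence behind the reward. That is plausible but not shown. All arms use the same order, but the result carries money in only some of them, so equal order does not guarantee equal influence.

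Third, taking CO first has a purpose. Table 2 names the share of CO readings completed as the primary outcome, and an early reading protects it. This is a fair reason not to move the reading, and it favours withholding the value over reordering.

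A reader might go further and infer that continuous abstinence and time to relapse are affected too. The documents do not support this. The only abstinence rule given uses CO alone, so under it a smoked day reading below 8 ppm counts as abstinent whatever is answered. No outcome is labelled self-reported abstinence.

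A reader might also infer that the order removes the means of checking CO against self-report. It does not. Self-report is still collected, clinic CO is measured at the visits, the exit survey asks about honesty, and the stated aim is the feasibility of remote testing, not its diagnostic accuracy.

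**Conclusion.** The point holds as a minor, conditional design weakness. It is certain that the CO reading precedes the tobacco items in the same session, and that CO results count toward payment only in the incentive arms. It is likely, but not stated, that participants see the reading. When they see it is not stated at all. If it is before the tobacco items, reported cigarettes per day is not independent of the CO result, and the dependence could differ by arm and, in the short-term arm, between weeks 1–6 and 7–12.

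It would be tempting to conclude that the paid arms under-report and that this would mimic an incentive effect. The documents do not establish that, and any percentage put on it would rest wholly on assumed rates. The exposure is confined to one secondary, exploratory outcome in a 60-person feasibility trial that describes itself as underpowered for cessation differences. The primary feasibility outcomes are unaffected by misreporting.

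**What to change.** State when the app displays the ppm value. If it is shown before the tobacco items, do one of the following in both country versions:

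- **Keep CO first and withhold the value** until the tobacco-use items are answered. This changes the display only and leaves CO capture as it is.
- **Ask two items immediately before the CO reading:** whether the participant smoked that day, and how many cigarettes. The participant then knows a test follows but not its result. The cost is a few seconds and possibly slightly lower CO capture, which bears on the primary outcome in Table 2.

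Either way, add a sentence stating that cigarettes per day is taken from answers given before the result is shown.

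The article gives May 31, 2019 as the anticipated end of recruitment, so the change may come too late for this trial. In that case, report whether and when the value was displayed, tabulate disagreement between CO and self-report by arm and payment window as description only, and set the order before the larger trial.

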#### Exit surveys and interviews

At visit 3, participants will complete a brief exit survey that includes 10 questions related to their experience in the study. Participants will be asked to rate the difficulty or ease of using the smartphone, the app, and the CO device and about their perception of accuracy of the CO readings. They will be asked about reasons for missing daily assessments, the difficulty or ease of this quit attempt, whether payments may have helped them or could help others to quit, and if they were honest and completed the assessments themselves as instructed. The qualitative interviews will use semi-structured topic guides to gather rich and in-depth information related to the participants’ motivation to take part in the study, their attitudes towards financial incentives, their experiences in the study submitting data, their overall quit attempt, any perceived impact on their diabetes, and suggestions for improvements to the study. The interviews will be carried out in-person or over the telephone according to the participant’s preference and every participant will be approached for recruitment for an interview. The interviews will be audio-recorded and transcribed verbatim.

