### Study procedures

At visit 1, the study coordinator will demonstrate the use of the smartphone and remote CO device and answer any questions related to the study procedures. After obtaining informed written consent, the study coordinator will measure height, weight, and CO and the participant will complete the baseline assessments using a REDCap survey on a tablet. At visit 2, 1 week after baseline, the participant will return to the clinic on their quit date. A study coordinator will provide instructions to the participant based on their random group assignment and will provide the participant with their smartphone and CO monitor. The participant will receive written instructions and training on how to use the smartphone and respond to the daily assessments. Participants will receive a 300-min unlimited data and text phone plan and will be permitted to use the phone for calls, text messages, and internet during the 12-week follow-up period to encourage participants to ensure the phone is charged and available at the time of each assessment. This will also be an incentive to submitting data since we are unable to compensate participants for submitting data. Participants will be asked on their preferred method of contact, which includes calls or text messages on their study phone or personal phone. A study coordinator will monitor their data weekly and contact participants throughout the 12-week daily assessment follow-up period to ensure that the phone is working and to answer any questions. Participants who enroll in the study at the baseline visit who miss their quit date and, therefore, do not receive a smartphone or CO monitor will be involuntarily withdrawn from the study if they are not able to reschedule within 1 week. Participants who wish to withdraw from the study at any time will be asked to return the smartphone and will be voluntarily withdrawn at the time of the request. Participants who withdraw from the study are offered the opportunity to provide feedback on the study prior to exiting. At visit 3, participants will complete the exit survey and exit interview and return the study phone and CO device to the study personnel.

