### Statistical methods

As this is a feasibility study, we will first examine our primary outcomes by calculating loss to follow-up rates for the follow-up visits and the proportion of daily assessments completed per participant for each study arm. We will also examine monthly recruitment and enrollment rates, and evaluate the acceptability of the program using the exit survey items. Although we are underpowered to test differences, we will explore the feasibility of our study protocol and data completeness by conducting statistical analyses similar to that of a larger trial. We will initially conduct range checks for data values to assess data quality. We will calculate descriptive statistics and compare baseline characteristics between arms to ensure adequate randomization between groups. All questionnaire items will be scored using methodology described in the literature. We will calculate means and standard deviations for continuous measures and frequencies for categorical measures. We will use time-to-event analysis to explore time to relapse and/or time to discontinuing the daily assessments. Smoking cessation assessment data and ecological momentary assessment data will be measured repeatedly and will therefore be correlated within subjects. Thus, our analytic approach will include generalized linear mixed model regression analysis. This analysis approach can handle normal and non-normal outcomes, such as dichotomous smoking status variables, different variance functions, as well as unbalanced designs where the number of repeated observations varies across individuals. Analyses will be conducted using both intention-to-treat and per-protocol approaches. All preliminary results will be interpreted with caution and treated as preliminary due to small numbers in each arm of this feasibility study. For the qualitative components of this study, we will use the transcribed interviews to develop codes and we will use thematic analysis to determine the feasibility and acceptability of this study protocol.

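### The survey part of acceptability is collected only from visit 3 attenders, so it is at risk of completer bias that may differ by arm

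*Protocol article*

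**What the plan says.** *Exit surveys and interviews* fixes the timing of the survey: "At visit 3, participants will complete a brief exit survey that includes 10 questions related to their experience in the study". *Study procedures* says the same, and Table 1 marks the exit questionnaire in the visit 3 column only. The survey covers ease of using the phone, app and CO device, reasons for missed daily assessments, and views on payments.

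*Feasibility outcome measures* makes it part of a secondary outcome: "acceptability of study procedures as measured in the exit survey and qualitatively in the exit interviews". *Statistical methods* plans to "evaluate the acceptability of the program using the exit survey items".

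Two other routes to participants' views are described.

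- Interviews: "every participant will be approached for recruitment for an interview", and "The interviews will be carried out in-person or over the telephone according to the participant’s preference" (*Exit surveys and interviews*). *Study procedures*, however, lists the exit interview with the survey at visit 3.
- Withdrawals: "Participants who withdraw from the study are offered the opportunity to provide feedback on the study prior to exiting" (*Study procedures*). No instrument is named.

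Reasons to attend visit 3 differ by group (*Intervention and control groups*). Earned incentives are handed over there as gift cards once the phone is returned. US controls enter a tablet draw on completing the 12 weeks and returning the phone. UK controls have neither.

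**The concern.** The survey asks why daily assessments were missed and how hard the technology was to use. Those answers explain a primary outcome, the proportion of daily assessments completed. The people with most to say on both are plausibly the least likely to attend visit 3. If so, the survey describes acceptability among those who tolerated the program, whereas the larger trial needs to know about smokers with type 2 diabetes who enter it.

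The *Discussion* itself raises possible differential drop-out in controls and says it will be evaluated within the acceptability and feasibility measures. The survey half of that check does not reach those who dropped out. Answers that were never collected cannot be recovered in the analysis.

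**Working it through.** **Step 1. Planned numbers.** *Participant eligibility and recruitment* gives 10 per arm at each of two sites. 2 sites × 3 arms × 10 = 60, which reproduces the stated target, with 20 per arm. The document gives no visit 3 attendance rate and no information on non-attenders' views.

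**Step 2. Which routes reach whom, as written.**

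| Participant | Exit survey | Interview | Other feedback |
|---|---|---|---|
| Attends visit 3 | Yes | Yes | – |
| Withdraws formally | No route stated | Approached under one section; at visit 3 under another | Offered, format unstated |
| Falls silent or misses visit 3 | No route stated | Same conflict | None stated |

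The withdrawal feedback appears in neither the outcome definition nor the analysis. The interviews are qualitative and do not supply the survey ratings.

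**Step 3. Size of a possible bias (all inputs assumed).** Let r be visit 3 attendance, and let a_att and a_non be the shares finding the study acceptable among attenders and non-attenders. The survey reports a_att, while the value for everyone is r × a_att + (1 − r) × a_non. Hence

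overstatement = (1 − r) × (a_att − a_non).

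Take a_att = 80% and a_non = 40%.

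- Incentive arm, r = 80% (16 of 20): 0.20 × 0.40 = 8 points.
- Control, r = 60% (12 of 20): 0.40 × 0.40 = 16 points.
- Difference between arms: 16 − 8 = 8 points.

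Keep a_att at 80%, and let r run from 40% to 90% and a_non from 20% to 80%.

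- Smallest: a_non = 80% gives 0 at any attendance.
- Largest: 0.60 × 0.60 = 36 points, at r = 40% and a_non = 20%.
- With attendance of 80% against 40% and a_non = 20%, the arms differ by 36 − 12 = 24 points.

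If non-attenders were the more favourable group, the sign would reverse.

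**Step 4. Bounds (assumed counts).** Suppose 40 of 60 attend and 36 of them are favourable. The survey gives 36/40 = 90% (exact 95% CI 76% to 97%). Over all 60, the value lies between 36/60 = 60% and (36 + 20)/60 = 93%. These bounds fall on both sides of 90%, so they show uncertainty and do not prove upward bias.

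**Step 5. Effect of reaching non-attenders.** With the first set of assumptions in Step 3, let half of the non-attenders answer the same items.

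- r = 80%: observed (0.80 × 0.80 + 0.10 × 0.40)/0.90 = 75.6%, true 72.0%, overstatement 3.6 points instead of 8.
- r = 60%: observed (0.60 × 0.80 + 0.20 × 0.40)/0.80 = 70.0%, true 64.0%, overstatement 6.0 points instead of 16.

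If all answer, it is 0.

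**The case against.** A reader might infer that acceptability is measured almost only in completers and is bound to look too good, differently by arm. The document does not support that, for these reasons.

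- The outcome also rests on interviews, for which one section approaches every participant, by telephone if preferred. Withdrawers are offered feedback, and the full protocol may name an instrument that the article omits.
- Loss to follow-up and daily assessment completion are primary outcomes reported by arm, so the selection would be visible.
- No between-arm comparison of acceptability is stated. In *Statistical methods*, the reference to each arm attaches to follow-up and daily assessments.
- The pull of visit 3 is not uniform. Only incentive-arm participants with at least one verified week have a card to collect, and US controls have the draw.
- The survey as described has no single overall acceptability proportion, so any such percentage is a device for illustration.

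All of this stands against the stronger reading. It does not close the gap. Reported attrition shows how many left but not what they thought, and the survey's timing and place in the analysis are stated in the article rather than left to another document. Surveying at the last visit is ordinary in a 60-person feasibility trial, which limits the severity.

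**Conclusion.** The point holds for the survey-based part of acceptability. That part comes only from visit 3 attenders and is at risk of completer bias, plausibly upward and possibly different by arm. The direction rests on the assumption that people who leave or stop responding like the program less than those who stay. The arm difference rests on the assumption that the unequal reasons to attend affect attendance. Neither can be checked from the document.

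The size is unknown and could be zero; the 0 to 36 point range is only what the assumed inputs produce. Separately, the two sections on interviews disagree on whether people who miss visit 3 are interviewed. Severity is minor to moderate: a named secondary outcome meant to inform a larger trial is affected, but the primary outcomes are not.

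**What to change.** 1. Offer the same 10 items by telephone or link at withdrawal, after daily assessments have stopped, or when visit 3 is missed. Use a personal contact route where the study phone has been returned, since withdrawers are asked to hand it back.
2. Report survey responders as n/N by arm, with best-case and worst-case bounds for non-responders.
3. For items on the phone, app and CO monitor, use participants who received the devices as denominator. Randomization precedes visit 2, and those who miss the quit date and cannot reschedule are withdrawn without a device. List them separately by arm, so that they are not counted as finding the devices unacceptable.
4. Reconcile *Exit surveys and interviews* with *Study procedures* on whether non-attenders are interviewed, and state whether withdrawal feedback counts towards the acceptability outcome.

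The cost is a few sentences in the protocol and a few extra contacts. Coordinators already follow participants up by their preferred method, and the visit surveys already run in REDCap. The downside is partial response among drop-outs, which would reduce the bias without necessarily removing it.
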